## Methods

### Aims

The primary aim of the trial is to determine whether the SystemCHANGE™ intervention is more effective than the attention control intervention in improving MA in adult kidney transplant recipients at the completion of the intervention and maintenance phases. We hypothesize adult kidney transplant recipients participating in the SystemCHANGE™ intervention will have higher immunosuppressive MA rates than those participating in the attention control at the completion of intervention and maintenance phases. A secondary aim is to examine the patterns of MA in this group. We will determine when the intervention becomes effective (e.g., what “dose” is needed) and what the pattern of decay in medication adherence is over time in both groups. Our exploratory aims are to determine whether the SystemCHANGE™ intervention is more effective than the attention control in decreasing poor health outcomes (e.g., infection, acute/chronic rejection, graft loss, death, and increasing creatinine/blood urea nitrogen,), to explore potential mediators (social support and systems-thinking) and moderators (ethnicity, perceive health and level of medication nonadherence) of MA, and to determine whether the SystemCHANGE™ intervention is cost-effective. We hypothesize patients in the SystemCHANGE™ intervention will demonstrate lower levels of poor outcomes than attention controls at 12 months. We also hypothesize the cost-effectiveness ratio for the SystemCHANGE™ intervention will be less than the cost-effective ratio for the attention-control intervention.

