Our primary analysis assesses whether the SystemCHANGE™ intervention is more effective than the attention-control intervention in increasing MA in adult kidney transplant recipients at the completion of the 6-month intervention and 6-month maintenance phases. We hypothesize that adult kidney transplant recipients receiving the SystemCHANGE™ intervention will have higher immunosuppressive MA rates than the attention-control group at the completion of intervention and maintenance phases. Since rate responses will most likely violate the normality assumption, the non-parametric method, Mann- Whitney test, will be used for comparing the two groups. However if the normal assumption is satisfied through transformation or as raw data measures, t-test will be applied for group comparison. Possible covariates resulting from demographic data and screening phase MA will be included in the analysis to adjust for possible bias.

Our secondary analysis assesses the MA patterns in both the SystemCHANGE™ and attention-control groups. Specifically we are interested in determining when the intervention becomes effective (e.g., what “dose” is needed) and the pattern of decay in MA over time in both groups. The dependent variable for these research questions are the repeated measurements of immunosuppressive MA rates at 12 time points [i.e. 1, 2, 3, 4, 5, 6, 7, 8, 9, 10, 11 and 12 months] and the independent variable is group assignment and time effect. Poisson regression analysis will be used for these questions. Proc Nlmixed procedure in SAS will be used for Poisson regression modeling. In order to answer the hypothesis we will test for group-by-time interaction to test if the two groups have different time profiles for MA or not. Possible covariates resulting from demographic data and screening phase MA will be included in the model to adjust for possible bias. Repeated measures from the same Pp will be accounted for using a random effect in the model.

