If this SystemCHANGE™ intervention is found to be effective in kidney transplant patients, other chronically ill populations known to have medication nonadherence (those with hypertension, diabetes, TB, asthma, epilepsy) may immediately benefit from this approach while trials are conducted to confirm findings across populations. The obdurate problem of medication nonadherence is rampant. Scientists’ medication nonadherence interventions will move from focusing primarily on interventions to change knowledge, attitudes, and beliefs and instead are focusing on changing the personal environment and shaping daily routines. Clinicians will cease blaming the patient for the inability to adhere to the prescription, but will, within the SystemCHANGE™ framework, support patient-designed, interventionist-guided, small experiments using Deming’s Plan-Do-Check-Act cycle [69] Our pilot study results indicate that the SystemCHANGE™ intervention “dose” may be effective immediately. If these results are supported in this larger study, clinicians could quickly and easily deliver the intervention in the hospital or clinic setting at a reasonable cost. Electronic monitoring systems are constantly improving. Wireless systems are streamlining electronic monitoring of medications, which further enhances the ease of delivery. The findings of this study may also prompt researchers to explore SystemCHANGE™ approaches to changing other important public health problems arising from human behavior (e.g. smoking).

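### The sole named test for the secondary questions, group-by-time interaction over months 1–12, is blind to a constant difference from month 1 and identifies neither onset month nor within-arm decay

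*Protocol article*

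**What the plan says.** All references are to the protocol article.

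- **Questions.** Aims sets the task: "We will determine when the intervention becomes effective", together with the pattern of decay over time in both groups. Statistical analysis repeats it: "we are interested in determining when the intervention becomes effective".
- **Outcome.** Statistical analysis defines the dependent variable as "the repeated measurements of immunosuppressive MA rates at 12 time points" and lists months 1 to 12. There is no month 0.
- **Model.** A Poisson regression with a random participant effect, in which "the independent variable is group assignment and time effect".
- **Screening adherence.** It enters only on the covariate side: "Possible covariates resulting from demographic data and screening phase MA will be included in the model to adjust for possible bias".
- **Test.** To answer the hypothesis, "we will test for group-by-time interaction to test if the two groups have different time profiles for MA or not". No test of the group term, joint test or monthly contrast is named for these questions.
- **Expected pattern.** Discussion says of the pilot that the intervention dose "may be effective immediately". Separately, the primary hypothesis in Aims expects higher adherence with SystemCHANGE at the end of both the intervention and the maintenance phase.

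**The concern.** An interaction test asks whether the difference between arms changes across the time points in the model. When every time point lies after the start of treatment, a gain already present at the first point that then persists does not change. It sits wholly in the group term. The trial's own statements make this case plausible: the pilot points to a fast onset, and the primary hypothesis expects a difference at both month 6 and month 12.

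There is also a mismatch between the test and the questions. A significant interaction says that the profiles are not parallel. It does not say in which month the arms first separate. If both arms decay at the same rate, it is null although decay is present in each.

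What is at stake is how the secondary aim is read. The Design section justifies the repeated measures by the wish to learn whether a shorter delivery would do, and the Discussion ties quick clinical delivery to an immediate effect. A non-significant interaction could be taken as no early effect when the effect was in fact at its earliest.

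**Working it through.** **1. The plan's own figure.** Inputs from Statistical analysis: difference 10 points, effect size 0.70, alpha 0.05 (taken as two-sided), power 90%, 46 per group.

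- n per group = 2(1.960 + 1.282)² / 0.70² = 43. An exact t-test needs 44.
- Dividing 43 by the Mann-Whitney efficiency 0.955 gives 45.03, rounded up to 46. This matches the stated size.
- Implied SD: 10 / 0.70 = 14.3 points.

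This sizing is for the 6-month comparison. No power is stated for the interaction test.

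**2. Formulas.** Let n = 46 per arm, T time points, δₜ the arm difference at month t with mean δ̄, σ = 0.143, and ρ the within-person correlation. The documents do not give ρ; it is assumed to lie between 0.3 and 0.9. Under a random-intercept model with no dropout:

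- interaction: λ_I = (n/2) Σ(δₜ − δ̄)² / [σ²(1 − ρ)], on T − 1 df;
- group effect: λ_G = (n/2) δ̄² T / {σ²[1 + (T − 1)ρ]}, on 1 df;
- joint test of both: λ_J = λ_I + λ_G, on T df.

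**3. Constant difference of 0.10 over months 1–12.** Every δₜ equals δ̄, so λ_I = 0 whatever the size of the benefit. At ρ = 0.9, λ_G = 23 × 0.01 × 12 / (0.0204 × 10.9) = 12.4. At ρ = 0.3, λ_G = 23 × 0.01 × 12 / (0.0204 × 4.3) = 31.5.

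**4. Other shapes.** Ramp: the difference rises linearly to 0.10 at month 6, then holds. Decay: 0.10 to month 6, then falls linearly to zero at month 12. Month 0: a 13th point with no difference is added to the constant case, which makes Σ(δₜ − δ̄)² = (12/13) × 0.01 = 0.00923.

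**5. Power, two-sided 0.05, time categorical.**

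| ρ | Planned test, constant | Group effect, constant | Planned test, ramp | Planned test, decay | Interaction with month 0, constant | Joint test (12 df), constant |
|---|---|---|---|---|---|---|
| 0.3 | 0.050 | >0.99 | 0.78 | 0.94 | 0.71 | 0.98 |
| 0.5 | 0.050 | >0.99 | 0.92 | 0.99 | 0.88 | 0.88 |
| 0.7 | 0.050 | 0.97 | >0.99 | >0.99 | 0.99 | 0.74 |
| 0.8 | 0.050 | 0.96 | >0.99 | >0.99 | >0.99 | 0.68 |
| 0.9 | 0.050 | 0.94 | >0.99 | >0.99 | >0.99 | 0.62 |

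The joint-test column uses a chi-square approximation and no adjustment for screening adherence.

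**6. Log scale.** The planned model has a log link, on which the zero interaction corresponds to a constant ratio. A simulation of 3,000 trials (control mean assumed 0.65, empirical variances) gave rejection of 0.055, 0.047 and 0.048 for the planned interaction at ρ = 0.5, 0.7 and 0.9. The group effect gave 0.99, 0.98 and 0.94.

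**The case against.** The test does what its sentence says. It asks whether the two time profiles differ, and for parallel curves not rejecting is the right answer. Effectiveness is the primary question and is tested separately at the end of each phase. The secondary model contains a group term in which a lasting early gain would appear, and with categorical time it could yield monthly differences and within-arm trajectories. Exact contrasts are often left to an analysis plan that is not shown here. The aim also looks for decay, and the table shows that the planned test detects an effect fading to zero, or one building up over six months, with good power.

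Most of this stands, and it limits the point. A reader might infer three stronger things that the documents do not support:

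- **That the pilot showed an immediate and sustained effect.** The Discussion says only that the dose may act immediately. Persistence comes from the trial's hypothesis for both phases, which concerns months 6 and 12 and does not itself promise a flat difference.
- **That the trial would miss a real benefit.** The primary comparisons do not use this test.
- **That the secondary analysis can never answer its questions.** The model could answer them; the named test alone does not.

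What does not stand is the appeal to detail left elsewhere. The article itself fixes the time points and names the interaction as the test that answers the hypothesis.

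**Conclusion.** The point holds in a limited form. With outcome points only at months 1–12, a difference that is constant from month 1 gives zero interaction, and the named test rejects at 0.05. That figure follows from the algebra and is not itself a measure of harm. The informative contrast is with the group effect, which has power of about 0.94 or more in the same data. The power figures assume 46 per arm, a 10-point difference, a common SD of 14.3 points, correlation 0.3–0.9 and no dropout; the zero interaction depends on none of these. For effects that ramp or fade to zero the test is valid and well powered (0.78 and 0.94 or more). In no case does it by itself identify the onset month or decay within an arm. The weakness is confined to the secondary aim, should be corrected there, and leaves the primary analysis untouched.

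**What to change.** Replace the sole interaction test by one of two options:

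1. Keep months 1–12 with categorical time, fix screening adherence as a covariate, and test group and group-by-time jointly. The covariate is already foreseen and does not alter the zero interaction; the joint test is the real change.
2. Model screening adherence as month 0 with a common mean for both arms, and then not also as a covariate. A common mean is reasonable because randomisation follows the same selection below 85%. Month 0 should have its own variance, since it summarises three months and is truncated by that selection.

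Under either option, report:

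- **Onset:** month-specific arm differences with simultaneous 95% confidence intervals, read as a description. A rule that dates onset to the first interval above zero would depend on power.
- **Decay:** the change from month 6 to months 7–12 within each arm, and the difference in that change between arms. The stated question concerns both groups.

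The variance model must suit a rate between 0 and 1. With plain Poisson variance, a simplified Wald interaction test rejected in 0% of simulated trials even with month 0 included, so adding a baseline point would not help on its own.

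The cost is analysis wording only, because screening adherence is already collected. Simultaneous intervals are slightly wider than unadjusted ones. The 12-df joint test also has less power against a constant effect than a 1-df group test (0.62–0.98 against 0.94 or more, before covariate adjustment), so the average group difference should be reported beside it.

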## Design

This is a 4-year, two-center, randomized controlled trial, that is single-blind (participants [Pps]) and uses a stratified sample block design with repeated measures. We are comparing the SystemCHANGE™ intervention to the attention control intervention in adult kidney transplant recipients with existing medication nonadherence documented by electronic monitoring. The repeated-measures design provides longitudinal data regarding medication nonadherence which allows us to determine when the intervention becomes effective (to determine if a lower dose of SystemCHANGE™, e.g. shorter time of delivery, is possible). It also allows us to track possible decay in medication nonadherence over time following the intervention.

We are examining the experimental effect on the outcome variable MA. During the 3-month screening phase, all Pps are using electronic monitoring to document medication taking. Those who are adherent (MA rate of .85 % or greater) exit the study. To prevent the “ceiling” effect, those with documented medication nonadherence (MA rate of less than .85 %) are stratified by low (<70 %), and moderate (70-84 %) nonadherence, based upon our previous medication nonadherence pattern research [41]. They then enter the intervention phase of the study and are randomized into either the treatment (SystemCHANGE™ intervention) or the attention control group (attention control condition). During the 6-month intervention phase, all Pps receive a home visit at baseline plus six telephone calls (at intervention months 1, 2, 3, 4, 5, 6). In addition, Pps randomized into the SystemCHANGE™ intervention are also guided in implementing SystemCHANGE™ activities related to medication taking by the Research Assistant (RA). Control group Pps receive RA-provided education guided by healthy living patient educational materials. The maintenance phase begins after the intervention and runs for an additional 6 months. This phase examines how Pps maintain MA in the absence of an intervention; however, we are continuing to use electronic monitoring to measure the outcome variable. Health outcome and healthcare cost data are collected during the intervention and maintenance phases.

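### The single group-by-time test over months 1–12 is not specific to decay and does not locate onset, the two questions it is named to answer

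*Protocol article*

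**What the plan says.** The Aims section sets two secondary questions: when the intervention becomes effective, and "what the pattern of decay in medication adherence is over time in both groups". The Design section places decay after treatment ends: "It also allows us to track possible decay in medication nonadherence over time following the intervention" (read here as decay in adherence, as in the Aims). On the phases it says: "The maintenance phase begins after the intervention and runs for an additional 6 months". Months 1–6 are therefore on intervention and months 7–12 are off it.

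The Statistical analysis section repeats both questions, including "the pattern of decay in MA over time in both groups", and gives them one model. The outcome is "the repeated measurements of immunosuppressive MA rates at 12 time points". On the model terms it says that "the independent variable is group assignment and time effect". The model is a Poisson regression, and "Repeated measures from the same Pp will be accounted for using a random effect in the model". The only test named is the interaction: "we will test for group-by-time interaction to test if the two groups have different time profiles for MA or not". No phase term, break at month 6, maintenance-phase contrast or within-group estimate of decay is named. Whether time enters as a trend or as 12 categories is not stated.

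**The concern.** Onset and decay belong to different phases, and the group difference may move in opposite directions in the two. One interaction over all 12 months asks only whether the two monthly profiles are parallel. They can fail to be parallel because a gain built up during the intervention, with no loss afterwards. They can be parallel while both groups decline, or while a gain that arrived at once is held throughout. A significant result is therefore not evidence of decay, and a non-significant one is not evidence against decay or against an early effect.

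At stake is the reading of the secondary aim: how much adherence is lost once support stops, and how short the intervention could be made.

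**Working it through.** **Inputs from the Protocol article (Statistical analysis).** Mean difference 10 points at six months, effect size 70 % (read as a standardised difference of 0.70), alpha .05 (taken as two-sided), power 90 %, 46 per group. Implied SD = 10 / 0.70 = 14.3 points.

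**The plan's own figure first.** n per group = 2 × (1.960 + 1.282)² / 0.70² = 42.9, so 43 by the normal formula and 44 by the exact t calculation. Dividing by the Mann-Whitney efficiency, 44 / 0.955 = 46.1, which is in line with the stated 46. The article gives no figure for the decay analysis.

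**Assumptions, not in the article.** A Gaussian model stands in for the Poisson mixed model. The 12 monthly group differences have covariance (2/46) × 14.3² × [ρ + (1 − ρ)φ^|j−k|], where ρ is the between-person share (0.5–0.7) and φ the month-to-month correlation of the remainder (AR(1), 0.5–0.6). The random-intercept-only version sets φ = 0, with ρ from 0.5 to 0.8. Power comes from the non-central distribution of each test: linear time × group (1 df), categorical time × group (11 df), and month 12 minus month 6 by group (1 df).

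**A worked case by hand (random intercept only, ρ = 0.5).**
- Variance of one monthly difference after removing the person effect: (2/46) × 204.1 × 0.5 = 4.44.
- Linear slope: the sum of (t − 6.5)² over months 1–12 is 143, so SE = √(4.44 / 143) = 0.176 points per month.
- Rise to 10 by month 6, then held: fitted slope difference +0.728, z = 0.728 / 0.176 = 4.1, power 98.5 %. True decay is zero.
- Rise to 10 by month 6, then fall to 0 at month 12: fitted slope difference −0.210, z = 1.2 in size, power 22 %.
- Month 12 minus month 6: SE = √(2 × 4.44) = 2.98. With a full loss, z = 10 / 2.98 = 3.4, power 92 %. With no loss, 5 %.

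**Rejection rates over the AR(1) range.**

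| True group difference | Linear × group | Categorical × group | Month 12 − month 6 |
|---|---|---|---|
| Rises to 10 by month 6, held (no decay) | 83–98 % | 63–90 % | 5 % |
| Rises to 10 by month 6, falls to 0 at month 12 | 11–17 % | 74–95 % | 92–99 % |
| Immediate 10, held to month 12 (no decay) | 5 % | 5 % | 5 % |
| Immediate 10, held to month 6, falls to 0 at month 12 | 95–99.9 % | 80–98 % | 92–99 % |
| Equal decay in both arms | 5 % | 5 % | 5 % |

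With a random intercept only, the first row becomes 98.5 % to over 99.9 % (linear) and 92 % to over 99.9 % (categorical). The second row becomes 22–47 % (linear) and 93 % to over 99.9 % (categorical). A simulation of 4,000 trials at ρ = 0.7 gave 99.98 % and 99.7 % for the first row, and 33 % and 99.8 % for the second.

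**What the table shows.** In the first row the test is significant under either coding with no decay. In the last row no between-group test can see the decay, so decay in each group needs a within-group estimate. In the third row the effect is present from month 1 and the interaction gives no sign of it, so onset has to be read from the monthly group differences themselves.

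**The case against.** **Coding and knots are usually left to a statistical analysis plan.** True, and the silence on coding is not the fault raised here. The article goes further: it names the model, the 12 time points and the test that is to answer the question, and that test does not match the question under either coding.

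**The failures depend on gradual onset.** The Discussion says the pilot suggests the effect may be immediate. With an immediate gain that is held, the interaction gives no false signal (5 %), and with an immediate gain lost by month 12 the linear test performs about as well as a maintenance contrast. This stands as a limit on the 83–98 % and 63–90 % figures. It does not rescue the test: gradual onset is not excluded, and immediate onset is the case in which the interaction says nothing about onset.

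**A reader might infer that a complete rise and fall would go undetected.** The documents do not support that in general. It holds only for linear time, which is not stated; twelve listed months and talk of profiles fit categorical time equally well, and that coding detects this pattern in 74–95 %. What it does not do is attribute the difference to the maintenance phase.

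**A reader might also infer that the trial cannot tell whether benefit persists.** That is not so. The primary analysis compares the groups at the end of both phases, so loss of the group difference by month 12 would show there.

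**The data would still show the profile.** The planned descriptive summaries and the fitted model can yield monthly estimates. This is right: the fault is in the named test, not in the data collected.

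**Conclusion.** The point holds for the secondary onset and decay questions only. The one test named for them is not specific to decay: with a gain that builds gradually to 10 points by month 6 and is fully held, it is significant in about 83–98 % (linear) or 63–90 % (categorical), and more often with a random intercept only. It is silent (5 %) on equal decay in both arms and on an immediate, sustained gain. Missing a full rise and fall is conditional on a linear trend (power 11–17 %, or 22–47 % with a random intercept only).

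The sizes rest on the article's 46 per arm and implied SD of 14.3, on assumed profiles and correlations, and on a Gaussian approximation. Under a Poisson model with its usual log link, equal decay means equal on that scale. That a parallel-profile test is neither a decay estimate nor an onset estimate needs none of these assumptions. The primary analysis and the sample size are not affected.

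**What to change.** In the secondary analysis:

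- State that time is fitted as monthly categories.
- Answer decay by the change from month 6 to month 12, within each group and between groups, with confidence intervals.
- Answer onset from the group differences at months 1 to 6.
- Keep the overall group-by-time test as a descriptive summary.

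A two-piece slope with a knot at month 6 can serve as a sensitivity analysis. It is less safe as the main answer: if the effect levels off by month 3 and nothing decays, it rejects in about 6–8 % (up to 15 % with a random intercept only), while the month 12 minus month 6 contrast stays at 5 %.

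The cost is analysis wording, with no new data and no change in sample size. The downside is slightly less power than a slope if decay really is linear: about 92–99 % against 95–99.7 % for a full loss of 10 points.

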### Primary outcome - medication adherence

Table 2 provides an overview of study measures and outcomes. The MA calculation method has been previously described but will be briefly described here [41]. A 0.5 is assigned if the dose of the immunosuppressive medication is taken within a 3-hour window (+/-1.5 hours of the prescribed time); 0.25 is assigned if the dose of the immunosuppressive medication is not within the 3-hour window but is taken within a 12-hour window (+/-6 hours of the prescribed time), and 0 is assigned if the dose of the immunosuppressive medication is not taken within a 12-hour window (+/-6 hours of the prescribed time, i.e., if the dose was missed). On each day, an individual is assigned a score of 0, 0.25, 0.50, 0.75 or 1 points (p. 526).

**Table 2 Tab2:** Study outcomes and measures

	Screening	Intervention	Maintenance
*Inclusion Criteria*			
6-item telephone measure of cognition	√		
Primary Outcome			
Medication adherence–electronic medication monitoring	√	√	√
Secondary Outcomes			
Creatinine	√	√	√
Blood urea nitrogen	√	√	√
Acute rejection	√	√	√
Chronic rejection	√	√	√
Infection	√	√	√
Death	√	√	√
*Potential Mediators*			
Social Support		√	√
Perceived Health		√	√
Personal Systems Thinking		√	√
*Background*/*Moderating Variables*			
Medical History	√		
Demographics (ethnicity)	√		
Level of Medication Nonadherence	√		
Pillbox use	√		
*Health care costs*			
Hospitalizations, clinic, observation, and ER visits	√	√	√

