### Statistical analysis

Sample size and power calculations are based on comparing expected change in medication adherence rate of patients in each group at six months - an expected adherence mean difference of 10 % based on our pilot study findings and the literature. We use an alpha of .05 and provide for 90 % power to detect indicated effect sizes in this two-arm randomized study. An effect size difference of 70 % is based on a conservative estimate of our pilot work. A sample size of 46 older KT recipients per group (final total sample 92) will meet these assumptions and provide sufficient power. Recruitment and retention rates are calculated from our pilot study, other adherence studies at the same sites, and are documented in one similar RCT adherence study in older KT recipients [63, 64]. We selected an adherence rate of 85 % to divide the adherers from the non-adherers based upon our preliminary work describing 4 clusters of KT medication adherers: those who (1) take medications on time (1.0-.85 MA rate), (2) take medications on time with late/missed doses (.84-.70 MA rate), (3) rarely take medications on time and who were late with morning and/or evening doses (.69-.20 MA rate), and (4) missed many doses (<.20). Even minor deviations in dosing adherence lead to poor outcomes, though no studies have determined the criterion adherence “dose” that distinguishes good and poor outcomes.

Appropriate descriptive analyses will be performed to examine distributional characteristics for collected measures, as well as to summarize changes over time as a function of group assignment. During this initial phase, we will explore bivariate relationships among primary and secondary outcome measures and variables thought to affect medication adherence. In addition, we will conduct analyses to determine whether the randomly assigned groups are equivalent at the start of the study on the demographic and other measures collected at baseline. Before hypothesis-testing analyses are conducted, exploratory analyses will be performed to examine the effect of various mediators and moderators on the relationship between intervention, adherence, and clinical outcome. The results of these analyses will determine what additional variables will be incorporated in the subsequent hypothesis testing (e.g., analysis of covariance).

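### The group-by-time test uses a Poisson model with a single random effect, so its standard error is uncalibrated and may be too large or too small

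*Protocol article*

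**What the plan says.** The Statistical analysis section sets out a secondary analysis whose outcome is the "repeated measurements of immunosuppressive MA rates at 12 time points", months 1 to 12. The method is named: "Poisson regression analysis will be used for these questions", run in SAS Proc Nlmixed. The test is named too: "we will test for group-by-time interaction to test if the two groups have different time profiles for MA or not". Within-person correlation is handled in one sentence: "Repeated measures from the same Pp will be accounted for using a random effect in the model". Screening-phase adherence and demographic variables may enter as covariates.

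The article does not say whether time is linear or a 12-level factor, or on what scale the rate enters the model. The section on the primary outcome builds the rate from daily scores between 0 and 1: "On each day, an individual is assigned a score of 0, 0.25, 0.50, 0.75 or 1 points". The Statistical analysis section also writes rates as proportions, for example "take medications on time with late/missed doses (.84-.70 MA rate". Elsewhere the same cut-offs appear as percentages.

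The only stated error rates belong to the 6-month comparison: "We use an alpha of .05 and provide for 90 % power". None is given for the interaction test.

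**The concern.** The interaction is a within-person contrast, and its standard error is right only if two things are modelled adequately.

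- **Within-person dependence.** A lone participant intercept makes months 1 and 2 as alike as months 1 and 12, and gives everyone in an arm the same trajectory. The intervention is individualised: participants choose their own solutions and are encouraged to try another if adherence does not improve. Varying trajectories are therefore to be expected.
- **Month-to-month variance.** A Poisson likelihood sets the variance equal to the mean. A monthly average of scores bounded by 0 and 1 does not follow that rule. The rule also depends on scale: the same data give different p-values as proportions and as percentages.

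This test answers when the intervention begins to work and how adherence decays. The Design section links the onset question to whether a shorter delivery is possible. Standard errors that are too small could produce an onset time or decay pattern from noise. Standard errors that are too large could hide a real difference between profiles.

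**Working it through.** **1. The plan's own figure, and the SD it implies.** The plan states a 10-point difference, an effect size of 70% (read as 0.70 SD), 90% power, alpha 0.05 (taken as two-sided) and 46 per group.

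- Normal formula: 2 × (1.960 + 1.282)² / 0.70² = 42.9, so 43 per group. The t-test needs 44.
- Dividing by the Mann-Whitney efficiency of 0.955: 44 / 0.955 = 46.1. The stated 46 reproduces, with power of 90.1%.
- Implied SD: 10 / 0.70 = 14.3 points, or 0.143 on the 0-1 scale (variance 0.0204).

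**2. Poisson variance against that SD.** At an assumed mean adherence of 0.70:

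| Scale | Poisson variance | Implied variance | Ratio |
|---|---|---|---|
| 0-1 | 0.70 | 0.0204 | 0.03 |
| monthly points out of 30 | 21 | 18.4 | 0.87 |
| doses out of 60 | 42 | 73.5 | 1.75 |
| percent | 70 | 204 | 2.92 |

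On the 0-1 scale inflation is impossible at this SD. Even if the variance of all 12 months fell into one time contrast, it would be at most 12 × 0.0204 = 0.245, below 0.70. Multiplying the outcome by 100 leaves log-rate slopes unchanged but divides their conditional Poisson standard error by √100 = 10.

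**3. Simulation of the stated model under no group difference.** Inputs: 46 per arm, 12 months and nominal 5% from the article. Assumed: mean 70 points, between-person SD 11.5, month-to-month SD 8 (together √(11.5² + 8²) = 14.0 points, close to 14.3), slope SD 0 to 1 point per month, and AR(1) 0 to 0.4. The model is a random-intercept Poisson in its conditional form, with 4,000 runs per row. Rejection rates in %, linear time unless noted:

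| Slope SD | AR(1) | 0-1 | out of 60 | percent | percent, 11-df test | clustered SE |
|---|---|---|---|---|---|---|
| 0 | 0 | 0.0 | 0.7 | 4.2 | 2.8 | 5.6 |
| 0.5 | 0 | 0.0 | 3.2 | 9.5 | 3.5 | 5.1 |
| 1.0 | 0 | 0.0 | 14.8 | 25.9 | 9.1 | 6.0 |
| 0 | 0.4 | 0.0 | 4.5 | 12.1 | 2.0 | 5.1 |
| 1.0 | 0.4 | 0.0 | 18.2 | 29.8 | 8.0 | 5.5 |

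The Monte Carlo standard error is about 0.3 points near 5% and 0.7 points near 25%. The clustered-SE column uses linear time and is the same on every scale.

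**4. Wider assumptions.** Here the monthly SD is 0.143, the intercept share of variance 0.4 to 0.8, the SD of person-specific 12-month change 0 to 1.4 times the monthly SD, and AR(1) 0 to 0.5.

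| Scale | Linear time | 11-df test |
|---|---|---|
| 0-1 | 0% | 0% |
| out of 30 | 0-26% | 0-2% |
| out of 60 | 2-42% | 0-17% |
| percent | 6-54% | 2-44% |

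The conditional form agreed with marginal maximum likelihood in 98-100% of 60 data sets on each of the three scales checked (0-1, out of 30 and percent).

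**5. Gaussian reference.** For a Gaussian random-intercept model with linear time, the ratio of true to model variance is (s² + 143b²) / (s² + 13b²), where b is the slope SD, s the month-to-month SD and 143 the sum of squared centred months. With s = 8, slope SDs of 0.3, 0.5, 0.8 and 1.0 give ratios of 1.18, 1.48, 2.15 and 2.69, and type I error of 7.1%, 10.8%, 18.1% and 23.2%. Under the assumptions of step 4, a Gaussian random-intercept model gives 4-37% for linear time and 4-12% for the 11-df test.

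**The case against.** - **The wording may be shorthand.** Referring to a random effect in the singular is common in articles and does not exclude a random slope, which Nlmixed can fit. The full plan may give the covariance structure. This stands as a reason for moderate confidence. It does not remove the point, because the article makes a positive choice (Poisson, one random effect, an interaction test), and a random slope would still leave the Poisson variance mismatched.
- **A reader might infer that the test simply has an inflated false-positive rate.** The documents do not support that. On the 0-1 scale, in which the score is defined, the test almost never rejects. On the 30-point scale the 11-df test stays at or below 2%.
- **A reader might carry the 7-23% of step 5 over to the planned model, or suppose inflation under any outcome distribution.** Those figures hold only for a Gaussian random-intercept model with linear time. A likelihood with a fixed mean-variance relation can be conservative instead.
- **Linear time is not stated.** Twelve listed time points fit a categorical reading equally well, and the 11-df test is less affected: 2-9% on the percent scale in step 3. It still reached 44% there under the wider assumptions, so categorical coding alone is not a safeguard.
- **The variability inputs are assumed.** Slope SD, month-to-month SD, AR(1) and mean adherence do not come from the article. The ranges show sensitivity and do not predict what this trial will see.

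**Conclusion.** The point holds in conditional form. With one participant intercept and a Poisson variance, the interaction test and the onset and decay contrasts lack a controlled error rate. Under slope SDs of 0 to 1 point per month, a month-to-month SD of 8 and AR(1) of 0 to 0.4, the nominal 5% linear test rejects about 0% on the 0-1 scale. On the percent scale it rejects about 4-25% with one departure at a time, and about 30% with both at their upper limits. Neither inflation nor conservatism can be asserted until scale and time coding are fixed. The result rests on reading the random effect as an intercept, a mean near 70 points and an SD near 14 points. It concerns a named secondary aim and should be corrected. The primary Mann-Whitney or t-test comparison does not use this model.

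**What to change.** State the outcome scale and treat month as categorical. Then obtain the group-by-time test and the onset and decay contrasts in one of two ways:

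- with cluster-robust (empirical) standard errors by participant, which held 5-6% for the linear contrast on every scale in step 3; with 92 participants and an 11-df test, a small-sample correction is advisable; or
- from a model with an unstructured within-person covariance, or a random intercept plus random slope with serial correlation, and a variance that is estimated and not fixed at the mean.

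Keep screening adherence as a covariate and add the randomisation stratum. Take onset and decay statements from the same fitted model.

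The cost is analysis wording and code. Data collection, conduct and sample size do not change. Intervals may widen where they are now too narrow; on the 0-1 scale they would narrow and power would be recovered.
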